# Reduction of corticosteroid use in outpatient treatment of exacerbated COPD - Study protocol for a randomized, double-blind, non-inferiority study, (The RECUT-trial)

**DOI:** 10.1186/s13063-019-3856-8

**Published:** 2019-12-16

**Keywords:** COPD, AECOPD, Exacerbation, Primary care, Corticosteroids

## Abstract

**Background:**

Chronic obstructive pulmonary disease (COPD) is a major public health issue affecting approximately 4% to 7% of the Swiss population. According to current inpatient guidelines, systemic corticosteroids are important in the treatment of acute COPD exacerbations and should be given for 5 to 7 days. Several studies suggest that corticosteroids accelerate the recovery of FEV1 (forced expiratory volume in 1 second), enhance oxygenation, decrease the duration of hospitalization, and improve clinical outcomes. However, the additional therapeutic benefit regarding FEV1 recovery appears to be most apparent in the first 3 to 5 days. No data are available on the optimum duration of corticosteroid treatment in primary-care patients with acute COPD exacerbations. Given that many COPD patients are treated as outpatients, there is an urgent need to improve the evidence base on COPD management in this setting. The aim of this study is to investigate whether a 3-day treatment with orally administered corticosteroids is non-inferior to a 5-day treatment in acute exacerbations of COPD in a primary-care setting.

**Methods/design:**

This study is a prospective double-blind randomized controlled trial conducted in a primary-care setting. It is anticipated that 470 patients with acutely exacerbated COPD will be recruited. Participants are randomized to receive systemic corticosteroid treatment of 40 mg prednisone daily for 5 days (conventional arm, *n* = 235) or for 3 days followed by 2 days of placebo (experimental arm, *n* = 235). Antibiotic treatment for 7 days is given to all patients with CRP ≥ 50 mg/l, those with a known diagnosis of bronchiectasis, or those presenting with Anthonisen type I exacerbation. Additional treatment after inclusion is left at the discretion of the treating general practitioner. Follow-up visits are performed on days 3 and 7, followed by telephone interviews on days 30, 90, and 180 after inclusion in the study. The primary endpoint is the time to next exacerbation during the 6-month follow-up period.

**Discussion:**

The study is designed to assess whether a 3-day course of corticosteroid treatment is not inferior to the conventional 5-day treatment course in outpatients with exacerbated COPD regarding time to next exacerbation. Depending on the results, this trial may lead to a reduction in the cumulative corticosteroid dose in COPD patients.

**Trial registration:**

ClinicalTrials.gov, NCT02386735. Registered on 12 March 2015.

## Background

In Switzerland, approximately 4% to 7% of the population suffer from chronic obstructive pulmonary disease (COPD), which is characterized by irreversible airflow obstruction and inflammation of the respiratory tract [1]. It is a progressive disease and its acute exacerbations are associated with increased morbidity and mortality. Thus, it is a major public health issue [2]. Data from a Swiss COPD cohort treated by general practitioners (GPs) demonstrated that approximately one in four COPD patients per year requires pharmacological treatment for an acute exacerbation of COPD (AECOPD) [3, 4]. Furthermore, a Spanish cross-sectional study found a median number of two exacerbations per patient per year in a population of 1001 COPD patients treated in general practice [5]. According to current guidelines, the inhalation of short-acting beta-adrenergic agonists and anticholinergic agents, as well as systemic glucocorticoids (GCs) is considered to be the standard therapy for AECOPD. The recommended daily treatment dose is 40 mg prednisone over 5 days [6, 7]. Several studies suggest that GCs accelerate the recovery of the forced expiratory volume in 1 s (FEV1), decrease the duration of hospitalization, reduce treatment failure, and improve clinical outcomes [8–14]. The additional therapeutic benefit regarding FEV1 recovery, however, seems to be most apparent during the first 3 to 5 days of GC treatment [8, 9].

The side effects of long-term GC treatment are well known, but even short-term treatment may cause adverse effects, such as secondary infections, hyperglycemia, or psychiatric symptoms [15]. Furthermore, repeated short-term applications of GCs result in high cumulative doses in the long term, which are associated with a higher vertebral fracture risk [16] and muscle weakness [17]. Whilst, there is strong evidence for the beneficial effects of GCs in the treatment of AECOPD, due to the potential serious adverse effects of GCs, coupled with a population base with frequent COPD exacerbations, a reduction in GC administration may be beneficial.

In our previous hospital-based study REDUCE, we found that a short 5-day treatment with systemic steroids was not inferior with regard to re-exacerbation compared to a conventional 14-day treatment in patients presenting to emergency departments with AECOPD [6]. These findings led to revisions of international guidelines [7]. However, even though many patients with AECOPD are treated as outpatients, no data are available about the minimal necessary duration of corticosteroid treatment in a primary-care setting. A shorter treatment duration may be advantageous in reducing long-term corticosteroid related side effects, as well as potentially being more cost-effective.

### Rationale

In this research project, we are focusing on optimizing the treatment of AECOPD in primary care, where the majority of patients are treated. The primary objective of this study is to investigate whether a 3-day treatment with orally administered systemic corticosteroids is non-inferior to a 5-day treatment for AECOPD in a primary-care setting. The primary endpoint is time to re-exacerbation. The study also aims to evaluate whether it is possible to minimize the cumulative dose of systemic GCs in patients suffering from AECOPD, without depriving them of the benefits of an optimal medication. A secondary objective is to evaluate differences between the two corticosteroid treatment durations regarding effectiveness and safety. Parameters to be evaluated as secondary endpoints are cumulative steroid dose, side effects and complications of GC treatment, change in FEV1, clinical course assessed through the COPD assessment test (CAT), need for hospitalization during the index exacerbation or during the follow-up, and death from any cause.

## Methods/design

### Study design and setting

The RECUT trial is a prospective randomized double-blind placebo-controlled non-inferiority trial in a primary-care setting. The coordinating study center is in Liestal, Switzerland, which is where the principal and co-principal investigators, study coordinators, and study physicians are based. The coordinating study center organizes all global activities in connection with the trial, is responsible for data management, and supervises endpoint adjudication. The trial steering committee is also based here. The study is conducted in collaboration with GPs in Northwestern and Central Switzerland, as well as in the Innsbruck area, Austria, who identify potential participants and perform study-related assessments. A list of participating GPs is available from the corresponding author on reasonable request.

Based on a sample size calculation, a total of 470 patients will be enrolled, with a 1:1 allocation ratio to the experimental and conventional arms. Participating GPs assess the eligibility of patients with AECOPD and perform any necessary diagnostic tests. Patients who fulfill the eligibility criteria and who are willing to participate receive 40 mg of oral prednisone per day for either 5 days (standard treatment group) or 3 days followed by 2 days of placebo (experimental group). Antibiotics (amoxicillin/clavulanic acid, 625 mg three times a day for 7 days) are administered to all patients with a serum C-reactive protein (CRP) level ≥ 50 mg/l at any of the study visits, and also to those with a known diagnosis of bronchiectasis or to those presenting with Anthonisen-type-I exacerbations [18]. Additional initial treatment and further treatments during the follow-up are determined and documented by the treating GP. Participants are assessed with respect to the primary and secondary endpoints after 3 and 7 days by their treating GPs. The coordinating study center contacts patients by phone for further evaluations on days 30, 90, and 180. If a patient cannot give sufficient information in the phone interview regarding the endpoints, then their GP is interviewed.

### Patient characteristics

The first patient was enrolled into the study in August 2015 and recruitment is expected to conclude by September 2021.

#### Inclusion criteria

To be included, patients must meet all of the inclusion criteria:
Age ≥ 40 yearsSigned informed consentHistory of ≥10 pack-years of smoking (past or present smokers)Airway obstruction, defined as FEV1 / forced vital capacity (FVC) ratio ≤ 70%Current AECOPD by clinical criteria, defined by the presence of at least two of the following:
Change of baseline dyspneaChange of coughChange of sputum quantity or purulence

#### Exclusion criteria

Patients are excluded if they meet any of the exclusion criteria:
Initial need for hospitalizationPrevious enrollment into the current studyAsthma/COPD overlap syndrome with a predominant asthma componentDiagnosis of tuberculosisSevere coexisting disease with life expectancy < 6 monthsKnown severe immunosuppression or immunosuppression after solid organ or stem cell transplantationInability to follow study procedures, e.g. due to language problems, psychological disorders, dementia, etc.Participation in another study involving an investigational drugWomen who are pregnant or breastfeedingPremenopausal women with insufficient contraception and anamnestic risk for pregnancy

### Blinding and randomization

Identical blister packs with daily doses of 40 mg prednisone for either 5 days (standard treatment arm) or 3 days followed by 2 days of placebo (interventional arm) are packed in a 1:1 ratio in the hospital pharmacy of the University Hospital Basel, Switzerland, in an environment regulated by Good Manufacturing Practice. Each blister pack is labelled with a computer-generated random alphanumeric code. A concealed envelope marked with this alphanumeric code on the outside contains the group allocation and is kept safe at the study center until the final data are analyzed. Depending on the expected number of eligible patients, each recruiting GP receives a certain number of the pre-randomized blister packs and hands them out to participating patients. Trial participants, GPs, outcome assessors, and data analysts are blinded to group allocation. Unblinding is permissible if necessary for the urgent medical treatment of a participant.

### Study intervention and assessments

The schedule of enrollment, interventions, and assessments is presented in Fig. 1. On day 1 (inclusion visit), the treating GP informs any patients presenting with AECOPD about the trial, checks their eligibility criteria, gets written informed consent, and performs a general clinical assessment including vital signs, dyspnea assessment (using the Modified British Medical Research Council Dyspnea Scale, mMRC), and CAT. A blood sample for CRP, plasma glucose, and leucocyte cell count is taken and FEV1 and FEV1/FVC are assessed by spirometry. Participating patients receive 40 mg of oral prednisone per day for either 5 days (standard treatment group) or 3 days followed by 2 days of placebo (experimental group). Any additional newly started exacerbation medication besides the study medication will be documented. Treating doctors can re-evaluate and change the treatment at any stage of the trial if necessary (e.g., if the patient’s clinical condition worsens). The implementation of either trial arm will not require any alteration in usual care. Thus, all concomitant treatments or medications considered necessary by treating doctors, including any newly started exacerbation medication, are permitted and their use will be recorded in the case report form (CRF).

**Fig. 1 Fig1:**
[figure not shown]
Summary of RECUT trial assessments performed at different time points. 1) Sex, age, weight, height, nationality, detailed medical history, CRP, plasma glucose, leucocyte cell count, respiratory rate, heart rate, blood pressure, pulse oximetry, body temperature, spirometry, mMRC, CAT, and quality and quantity of sputum and coughing. 2) All variables in 1) except demographic variables, but in addition treatment failure, hospitalization, mortality, change in medication, cumulative GC dose, clinically manifested side effects of GC or other medication. CAT only on day 7. 3) mMRC, CAT, quality and quantity of sputum and coughing, re-exacerbation, hospitalization, mortality, change in medication, cumulative GC dose, and clinically manifested side effects of GC or other medication. 4) Intervention (COPD self-management, smoking cessation), comments, and if lost to follow-up. CAT COPD assessment test, COPD chronic obstructive pulmonary disease, CRP C-reactive protein, GC glucocorticoid, mMRC Modified British Medical Research Council Dyspnea Scale

Follow-up visits will take place on day 3 (±1 day) and day 7 (±1 day) and each consists of a general clinical assessment, a blood sample, and an assessment of the clinical course regarding treatment failure and need for hospitalization. Furthermore, any changes in medication (including COPD baseline medication and exacerbation medication), cumulative GC dose, other interventions such as COPD self-management and smoking cessation, as well as clinically manifested side effects of GCs will be documented. During the second follow-up visit on day 7, a detailed medical history with regard to COPD is recorded and spirometry is performed. Participants are then followed up by phone on days 30, 90, and 180 after inclusion into the study (±7 days each). The phone interviews include dyspnea (mMRC) and CAT questionnaires, as well as questions regarding sputum, coughing, any changes in medication, and hospitalizations in the intervening time to assess re-exacerbation.

Participants may withdraw from the study at any time. Patients who prematurely withdraw from the study are nonetheless encouraged to attend the follow-up appointments. All data collected will be analyzed in an intention-to-treat analysis.

Since this study aims to evaluate a real-life situation in an outpatient setting as closely as possible and needs to be simple with regard to feasibility, patients’ adherence is not assessed. Patients are encouraged to return empty blisters to their GPs, which will be used to check whether they did take their medication according to the treatment plan. Poor compliance concerning the study medication is reported to the local study center and the coordinating center.

### Outcomes

The primary endpoint is time to next exacerbation during the 6-month follow-up period, which includes re-exacerbation during the index exacerbation (i.e. treatment failure). Exacerbation is defined as acute-onset worsening of the patient’s condition beyond day-to-day variations requiring interaction with a healthcare provider [19]. We chose time to next exacerbation as our primary endpoint to evaluate the effectiveness of the shorter steroid treatment. According to Leuppi et al. [6], Niewoehner et al. [9], and Aaron et al. [10], who investigated treatment failure rates, relapse rates, and time to relapse in AECOPD patients taking GCs, time to next exacerbation (which includes treatment failure) seems to be a valid measurement of effectiveness.

Secondary study outcomes are the cumulative GC dose, side effects and complications due to the GCs, change in FEV1, hospitalization rate during the index exacerbation and during the follow-up, clinical outcomes assessed by CAT and mMRC, as well as overall mortality. Cumulative GC dose and GC side effects are assessed to investigate the safety of short-term and standard steroid treatment. Furthermore, the change in FEV1, hospitalization rate during the index exacerbation and during the follow-up, as well as clinical outcomes and overall mortality are evaluated to compare the effectiveness of different durations of systemic corticosteroid treatment.

### Statistical analysis

It is hypothesized that the experimental treatment (3 days of corticosteroid treatment) is non-inferior to the conventional treatment (5 days of corticosteroid treatment) with regard to the primary endpoint. For this, a Cox proportional hazards regression model will be fitted to the data. Non-inferiority will be concluded if the two-sided 95% confidence interval of the hazard ratio between the experimental and the control arm lies entirely below the critical hazard ratio, which is defined as
$$ HR=\frac{\lambda_e}{\lambda_c}=\frac{\frac{-\log \left({\pi}_{et}\right)}{t}}{\frac{-\log \left({\pi}_{ct}\right)}{t}}=\frac{\log \left({\pi}_{et}\right)}{\log \left({\pi}_{ct}\right)}=\frac{\log \left({\pi}_{ct}-m\right)}{\log \left({\pi}_{ct}\right)} $$

where *t* is a fixed point of time, *λ*_*e*_ and *λ*_*c*_ are the hazard rates, *π*_*et*_ and *π*_*ct*_ are the proportions of event-free patients at time *t* in the experimental and conventional arms, respectively, and *m* is the non-inferiority margin, expressed as the additional proportion of patients having had an event in the experimental arm, assuming that the occurrence of events follows an exponential distribution [20]. This approach is partly based on the methodology described in a previous study undertaken by our research group [6, 21]. Following the recommendations of the Committee for Medicinal Products for Human Use, a two-sided 95% confidence interval is used to assess non-inferiority [22]. If there are missing data, GPs will be contacted by the study team with the aim of completing patients’ records, since data imputation is not planned. All statistical analyses will be performed on the per-protocol data set, complemented by a sensitivity analysis based on the intention-to-treat data set. Subgroup analyses or interim analyses are not planned.

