### Sample size calculation

When estimating the sample size, we assumed an exacerbation rate of 30% to 40% following an exponential distribution and a 15% drop-out rate evenly distributed within the 6-month follow-up period, for both the interventional and the conventional arms. The non-inferiority margin was defined as a 15% increase of the exacerbation rate within 6 months. The significance level was chosen to be 5% and the power 80%. A simulation and a Cox proportional hazards regression model were used to determine hazard ratios and 95% confidence intervals for the simulated data sets, which led to a sample size of *N* = 466 (95% confidence interval 461–471) for an exacerbation rate of 30%, and *N* = 464 (95% confidence interval 459–469) for an exacerbation rate of 40%, respectively. Therefore, we aim to recruit *N* = 470 patients into the study. The sample size will be re-estimated after approximately half of the initially estimated number of patients have reached the 6-month follow-up. If necessary, the sample size will be increased. We will re-estimate the exacerbation rates in a blinded manner, based on the overall observed exacerbation rate as described by Friede et al. [23]. Since no hypothesis test will be performed, no *p*-value adjustment to control the type I error rate is needed. If it is anticipated that enrolment goals will not be met, a geographical expansion of the study will be considered.

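### Two sections name different analysis populations for the primary non-inferiority decision, and the statistical section lets the per-protocol result alone support the claim

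*Protocol article*

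**What the plan says.** - Statistical analysis section, on populations: "All statistical analyses will be performed on the per-protocol data set, complemented by a sensitivity analysis based on the intention-to-treat data set".
- Study intervention and assessments section, at the end of the paragraph on withdrawal: "All data collected will be analyzed in an intention-to-treat analysis".
- Statistical analysis section, on the decision, which is taken against a critical hazard ratio: "Non-inferiority will be concluded if the two-sided 95% confidence interval of the hazard ratio between the experimental and the control arm lies entirely below" that value. One interval decides. No role is given to an ITT result that disagrees.
- Outcomes section: the primary endpoint is time to next exacerbation, "which includes re-exacerbation during the index exacerbation (i.e. treatment failure").
- Study intervention and assessments section: "Treating doctors can re-evaluate and change the treatment at any stage of the trial if necessary", with clinical worsening as the example. The same section says of patients that "adherence is not assessed". Returning empty blisters is encouraged, and poor compliance is reported to the study centers.

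**The concern.** Both population sentences are universal in wording: one covers all data, the other all analyses. Someone following the first would take the primary hazard ratio from every randomised patient. Someone following the second would take it from a subset and keep ITT as a sensitivity check. If the two results fall on opposite sides of the critical hazard ratio, the article supports either conclusion, and the statistical section read alone supports the claim.

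The choice matters here because a per-protocol set is formed after randomisation. The arms differ only on days 4 and 5. A patient who fails then may have treatment changed and may not finish the blister. If such patients left the per-protocol set, their primary events would leave with them. Should that happen more often in the 3-day arm, the hazard ratio would move towards non-inferiority.

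**Working it through.** **1. Inputs.** From Sample size calculation: "we assumed an exacerbation rate of 30% to 40% following an exponential distribution and a 15% drop-out rate", spread evenly over 6 months; "The non-inferiority margin was defined as a 15% increase of the exacerbation rate within 6 months"; 5% significance, 80% power, 470 patients. From Statistical analysis: the critical hazard ratio (HR) formula and the two-sided 95% interval.

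**2. The plan's own figures.** Critical HR = log(1 − p − 0.15) / log(1 − p), where p is the control-arm 6-month rate.
- p = 0.30: log 0.55 / log 0.70 = 1.676
- p = 0.35: log 0.50 / log 0.65 = 1.609
- p = 0.40: log 0.45 / log 0.60 = 1.563

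Events by Schoenfeld's formula: 4 × (1.960 + 0.842)² / (ln HR)².
- p = 0.30: 118 events; 118 / 0.30 / 0.85 = 463 patients (plan: 466)
- p = 0.40: 158 events; 158 / 0.40 / 0.85 = 465 patients (plan: 464)

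The stated sample size is reproduced closely, so margin and error rate are read as the plan intends. The point does not dispute the sample size.

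**3. How many events can days 4-5 supply?** Take p = 0.35, a 3-day-arm risk at the margin (0.50), 235 per arm, exponential times over 180 days, ignoring drop-out. Expected events on days 4-5 = 235 × [exp(−3λ/180) − exp(−5λ/180)].
- 3-day arm, λ = −ln 0.50 = 0.693: 1.8
- 5-day arm, λ = −ln 0.65 = 0.431: 1.1
- Difference: 0.7 of a patient
- All events to day 5 in the 3-day arm: 235 × [1 − exp(−5 × 0.693/180)] = 4.5

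**4. False non-inferiority rate on the per-protocol set alone.** Simulation at the margin: 470 patients, exponential times, 15% drop-out spread evenly, Cox model, 6000 trials per control rate. The nominal rate is 2.5%. Monte Carlo standard error is about 0.2 points near 2.5% and 0.4 near 11%.

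| Patients removed from the per-protocol set | p = 30% | 35% | 40% |
|---|---|---|---|
| None | 2.3% | 2.5% | 2.5% |
| Day 4-5 events, both arms | 2.2% | 2.5% | 2.5% |
| All events to day 7, both arms | 2.3% | 2.5% | 2.5% |
| Day 4-5 events, 3-day arm only | 2.8% | 3.1% | 3.4% |
| 5 earliest events, 3-day arm only | 4.7% | 4.7% | 5.2% |
| 7 earliest events, 3-day arm only | 5.9% | 5.9% | 6.5% |
| 12 earliest events, 3-day arm only | 11.2% | 11.3% | 11.1% |

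Repeat runs put the 5-patient row between about 4% and 5%. At p = 35%, the mean HR (geometric) falls from 1.61 with no removal to about 1.45 with 12 removed.

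**5. Requiring both sets.** When the ITT interval must also lie below the critical HR, the rate is at or below about 2.5% in every row (1.8% to 2.5%).

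**The case against.** Per-protocol as the primary set, with ITT alongside, is a recognised choice for non-inferiority, because non-adherence can pull an ITT hazard ratio towards 1. ITT is prespecified here and would show a discrepancy. The ITT sentence closes a paragraph on withdrawal and may mean only that withdrawn patients' data are kept for the ITT analysis, which the statistical section does plan. Patients, GPs, outcome assessors and analysts are blinded, so nobody can knowingly exclude by arm. Treatment changes on worsening are permitted, so they need not be protocol deviations.

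Most of this stands, and it limits the point. The withdrawal context softens the contradiction but does not remove it: the sentence is not restricted to withdrawn patients, and even read narrowly it keeps patients whom the per-protocol set may drop. Blinding prevents knowing exclusion by arm. It does not prevent unequal exclusion if the shorter course itself causes the deviations.

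A reader might infer that the plan will inflate the error to 5% or 11%. The documents do not support that. Those rates need a net loss of 5 to 12 event patients from one arm, against an expected excess of under one patient on days 4-5. A strong early excess of failures in the 3-day arm could supply more, but the plan assumes exponential times and gives no such pattern. A reader might also infer that per-protocol-primary is an error in itself, or that the set is undefined. Neither follows: the first is an accepted design, and the definition may stand in the full protocol or SAP.

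**Conclusion.** The contradiction holds on the wording and needs no simulation: two sections assign the single confirmatory comparison to different populations, and the statistical section gives a discordant ITT result no part in the decision. It must be reconciled before unblinding.

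The bias is possible, not shown, and alone would not make this a mandatory correction. The false non-inferiority rate stays near 2.5% if exclusions apply alike in both arms, is about 3% if only the 3-day arm's day 4-5 events are lost, and is about 4% to 11% under an assumed net one-arm loss of 5 to 12 event patients. These figures assume exponential event times, control rates of 30% to 40%, 15% evenly spread drop-out and a true effect exactly at the margin. The exclusion counts are assumptions throughout.

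**What to change.** Replace both sentences with one rule: non-inferiority is concluded only if the upper limit of the two-sided 95% interval lies below the critical hazard ratio in both the ITT set (all randomised patients, as randomised) and the per-protocol set. Keeping per-protocol in the rule guards against dilution of the ITT result by non-adherence.

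Add, or confirm if the full protocol or SAP already says so, that no patient leaves the per-protocol set because of a primary event or because of a treatment change prompted by one.

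The cost is wording, plus a small loss of power: at most about 2 percentage points against per-protocol alone when exclusions were equal across arms. The article reports recruitment as ongoing and allocation as concealed until the final analysis, so the change could be made blind.

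### Per-protocol is made the main set for every analysis, including side effects, hospitalisation, death and steroid dose, while another sentence promises intention to treat for all data

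*Protocol article*

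**What the plan says.** Protocol article, Statistical analysis: "All statistical analyses will be performed on the per-protocol data set". The sentence goes on to add ITT as a sensitivity analysis, and it makes no exception for any outcome.

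Protocol article, Study intervention and assessments, in the paragraph on withdrawal after Fig. 1: "All data collected will be analyzed in an intention-to-treat analysis".

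Protocol article, Outcomes: "Secondary study outcomes are the cumulative GC dose, side effects and complications due to the GCs, change in FEV1, hospitalization rate during the index exacerbation", followed by hospitalisation during follow-up, CAT, mMRC and overall mortality. The purpose of two of these is stated: "Cumulative GC dose and GC side effects are assessed to investigate the safety of short-term and standard steroid treatment". Hospitalisation, FEV1, clinical outcomes and mortality are grouped there as measures of effectiveness.

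The article does not define the per-protocol set. Three statements bear on who might fall outside it:
- The treating doctor's freedom: "Treating doctors can re-evaluate and change the treatment at any stage of the trial if necessary".
- Concomitant treatments, "including any newly started exacerbation medication, are permitted and their use will be recorded in the case report form".
- Adherence: "patients’ adherence is not assessed". Patients are only encouraged to return empty blisters, but those returned are checked, and poor compliance is reported.

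**The concern.** A per-protocol analysis has a recognised role in a non-inferiority comparison, because non-adherence can make two regimens look alike and so favour the non-inferiority claim. In this article that hypothesis is attached to one endpoint, time to next exacerbation. Side effects, hospitalisation, death and cumulative dose are compared to see whether the arms differ, and the same argument does not carry over to them.

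For those outcomes, a set chosen by behaviour after randomisation is no longer a randomised comparison. The choice can also depend on the outcome. A patient who stops the blister because of a steroid side effect has not followed the treatment plan, and under an adherence-based definition would leave the main side-effect analysis for that very reason.

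This matters because fewer side effects and a lower cumulative dose are, with possible cost savings, the article's stated reasons for wanting a shorter course (Background and Discussion). These are the results that should rest on the firmest comparison.

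**Working it through.** The article gives no size for the per-protocol set and no exclusion rate, so there is no figure of its own to reproduce here. The sample sizes of 466 and 464 concern the primary endpoint and do not depend on this point.

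**1. The two rules side by side.**

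| Place | Main set | Role of the other set |
|---|---|---|
| Statistical analysis | Per-protocol, for all analyses | ITT as sensitivity analysis |
| Study intervention and assessments | ITT, for all data collected | Not mentioned |

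Both are worded as covering everything. For the secondary outcomes they lead to different main analyses unless the second is read as describing only the sensitivity analysis, which it does not say.

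**2. Cumulative dose.** Inputs from Study design and setting: 40 mg daily for 5 days, or for 3 days followed by 2 days of placebo.
- Standard arm: 5 × 40 = 200 mg. Experimental arm: 3 × 40 = 120 mg. Planned difference: 200 − 120 = 80 mg.
- If a share q of each arm receives D mg of additional steroid, the difference over all randomised patients is 80 − D × (q_exp − q_std).
- Assume D = 200 mg (not in the documents):

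| q_exp | q_std | Difference, all randomised | Difference if those patients are dropped |
|---|---|---|---|
| 10% | 10% | 80 mg | 80 mg |
| 15% | 10% | 80 − 200 × 0.05 = 70 mg | 80 mg |
| 20% | 10% | 80 − 200 × 0.10 = 60 mg | 80 mg |
| 10% | 20% | 80 + 200 × 0.10 = 100 mg | 80 mg |

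Dropping these patients returns the comparison to the 80 mg fixed by design. That could overstate or understate the real saving.

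**3. Events outside the main set.** Assume that a fraction f of patients is excluded and that their risk is k times that of those kept. The share of all events still in the per-protocol set is (1 − f) / (1 − f + f·k):

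| f | k = 1 | k = 2 | k = 3 |
|---|---|---|---|
| 5% | 95.0% | 90.5% | 86.4% |
| 10% | 90.0% | 81.8% | 75.0% |
| 15% | 85.0% | 73.9% | 65.4% |

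These are pooled figures. They show how much information leaves the main analysis, not a bias between arms.

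**4. The contrast between arms.** With the same k in both arms, the per-protocol risk ratio equals the true ratio × (1 − f_std + f_std·k) / (1 − f_exp + f_exp·k).
- Equal exclusion (f_exp = f_std): the ratio is unchanged.
- k = 2, f_exp = 5%, f_std = 15%: 1.15 / 1.05 = 1.10, so a true ratio of 1 reads as 1.10.
- k = 2 with the fractions reversed: 1.05 / 1.15 = 0.91.

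The bias therefore depends on unequal exclusion and can go either way. Both arms receive the same blinded treatment for 3 days, so exclusion caused by a difference in treatment could begin only from day 4.

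**The case against.** The case against has real weight, on five counts.

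- **ITT is planned.** The sentence that sets the per-protocol rule also promises an ITT sensitivity analysis. Excluded patients would reappear there, and the Safety and data security section has all adverse events recorded whatever the analysis set.
- **The set is undefined here.** Its definition commonly sits in the full protocol or analysis plan, neither of which is shown. A reader might infer that the per-protocol set removes everyone who is hospitalised, dies or receives additional steroid. The documents do not support that. Changes of treatment and new exacerbation medication are permitted, and treatment failure counts as a primary event, so a set that dropped such patients would delete primary events.
- **The direction is unknown.** A reader might also infer that harm is under-counted in one arm or that the dose saving is overstated. Either needs unequal exclusion, or unequal additional steroid combined with exclusion of those patients. Neither is shown.
- **The window is short.** Study medication lasts 5 days, whereas hospitalisation and death are followed to day 180. Later events in patients who finished the blister would stay in.
- **Not all these outcomes are labelled safety.** Only cumulative dose and side effects are. Hospitalisation and mortality are called effectiveness.

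These points limit what can be said about consequences. They do not change the priority of the sets: the Statistical analysis section makes per-protocol the main one for every outcome. That is a stated rule, not a detail left to another document. A sensitivity analysis does not repair it, since the main result for side effects and dose would still come from the selected set. The effectiveness label does not bring hospitalisation and mortality under the non-inferiority hypothesis either. Nor does the lack of adherence assessment help: it leaves membership of the main set partly unobserved.

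**Conclusion.** The point holds as a fault in the stated rule and a conflict between two sections. Per-protocol is the main set for side effects, hospitalisation, death and cumulative GC dose, although the reason for it applies only to the primary endpoint, and another sentence assigns all data to ITT.

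The one size that rests on the documents is the 80 mg dose difference fixed by design, towards which a per-protocol comparison can drift if patients whose treatment was changed are excluded. The other figures above depend on assumed exclusion rates, risk ratios and additional doses, and only illustrate the mechanism. The most plausible route to exclusion by outcome is stopping the blister for a side effect, and even that assumes an adherence-based definition. It cannot be concluded that harm will be hidden or that the saving will be overstated. This should be corrected, but it does not threaten the primary analysis.

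**What to change.** 1. Reconcile the sentence under Study intervention and assessments with the one under Statistical analysis, so that each outcome has one named main set.
2. Limit the main role of the per-protocol set to the primary non-inferiority comparison.
3. For side effects, hospitalisation and death, make all randomised patients who took at least one dose the main set. As blister return is only encouraged, state how a patient is counted when intake is not documented.
4. For cumulative GC dose, FEV1, CAT and mMRC, make ITT the main set.
5. Keep per-protocol results for these secondary outcomes at most as a sensitivity analysis.

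The cost is wording in the protocol and analysis plan and a little analysis work. No new data are needed: the case report form and follow-up already cover these outcomes, and withdrawn patients are encouraged to attend follow-up. The change can be made while the allocation is still concealed.
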